### Follow-up

The primary outcome is 3 months.

### Protection against bias

#### Selection bias

Randomisation will be performed centrally using automated randomisation software. Randomisation will be performed after collection of baseline data, and concealment of allocation will be complete, as there will be no way for either researchers or participants to know which arm a participant will be allocated to until after allocation.

#### Performance and detection bias (blinding)

Participants will not be aware that they are part of a trial. The consent information will indicate that the research focuses on how best to provide online health promotion at work, and will not mention alcohol specifically. As all data collection relies on either self-report or automated data collection researchers will be unable to affect responses at follow-up.

#### Attrition bias

Every effort will be made to maximise the response rates for follow-up data. Particular efforts will be made to ensure high response rates for the primary outcome.

#### Reporting bias

The trial protocol will be published. Analyses will follow the intention to treat principle and will be pre-specified.

### Sample size

736 participants in each arm at 3 month follow up gives us 90% power with 5% significance to determine a 20% reduction in alcohol consumption. Allowing for up to 25% loss to follow-up at 3 months we will need to randomise 920 participants to each group (n 1,840); however we will take extensive steps to minimise loss to follow-up as described above.

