**Methods/design:**

Individually randomised controlled trial to determine the effectiveness and cost-effectiveness of offering online screening and brief intervention for alcohol misuse in a workplace. Participants: adults (aged 18 or over) employed by participating employers scoring 5 or more on a three item screen for alcohol misuse (the AUDIT-C) indicating possible hazardous or harmful alcohol consumption, recruited through the offer of an online health check providing screening for a range of health behaviours with personalised feedback. Participants who accept the health check and score 5 or more on the alcohol screen will be randomised to receiving immediate feedback on their alcohol consumption and access to an online intervention offering support in reducing alcohol consumption (*Down Your Drink*) or delayed feedback and access to *Down Your Drink* after completion of follow-up data at three months. All employees who take the online health check will receive personalised feedback on other screened health behaviours including diet, physical activity, smoking, and body mass index. The primary outcome is alcohol consumption in the past week at three months; secondary outcomes are the AUDIT, EQ-5D, days off work, number and duration of hospital admissions, costs and use of the intervention. A sample size of 1,472 participants (736 in each arm) provides 90% power with 5% significance to determine a 20% reduction in alcohol consumption. Outcomes between groups at three months will be compared following the intention to treat principle and economic analyses will follow NICE guidance.

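### Randomising 920 per arm does not allow for 25% loss: it leaves 690 per arm, not the 736 that the 90% power claim needs

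*Protocol article*

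**What the plan says.** The Sample size section of the protocol article makes two linked statements.

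- The number needed with outcome data: "736 participants in each arm at 3 month follow up gives us 90% power with 5% significance", for a 20% reduction in alcohol consumption.
- The number to randomise so that this many remain: "Allowing for up to 25% loss to follow-up at 3 months we will need to randomise 920 participants to each group (n 1,840").

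The section adds that extensive steps will be taken to keep losses down. The abstract (Methods/design) repeats the power claim for the followed-up total only: "A sample size of 1,472 participants (736 in each arm) provides 90% power with 5% significance to determine a 20% reduction in alcohol consumption". It does not mention the 1,840 to be randomised.

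**The concern.** Loss to follow-up is a proportion of those randomised. To have 736 left after losing a quarter, 736 must be divided by the retained share, 0.75. The stated 920 is what results if a quarter of 736 is added to 736 instead. The target, the tolerated loss and the number needed for 90% power therefore cannot all be true.

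The randomisation target is the figure that tells the team when recruitment may stop. A team that stops at 1,840 and then loses 25% would have stayed within the loss the plan says it allows for, and could reasonably believe that the planned power was kept.

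Losses of that order are not remote. The Discussion (Advantages and disadvantages of online trials) names low follow-up as a weakness of online trials, and the Data collection section plans several rounds of e-mail, post and telephone contact to counter it.

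**Working it through.** **Inputs, all from the Sample size section**

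- Needed with 3-month data: 736 per arm (the abstract agrees: 1,472 = 2 × 736).
- Power 90%, significance 5%. Sidedness is not stated; two-sided is assumed below and one-sided is shown as a check.
- Effect: 20% reduction. No mean or standard deviation is given.
- Loss: up to 25%.
- To be randomised: 920 per arm, 1,840 in total.

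**Step 1. Reproduce the stated 920**

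- 736 × (1 + 0.25) = 920. This matches exactly, but it is not the right formula for 25% loss.
- 736 / (1 − 0.20) = 920. This also matches exactly, and is the right formula for 20% loss.

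The margin of 920 − 736 = 184 is 25% of the 736 followed up, but 20% of the 920 randomised.

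**Step 2. Number required for 25% loss**

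- 736 / (1 − 0.25) = 981.3, rounded up to 982 per arm, or 1,964 in total.
- Shortfall in the stated target: 982 − 920 = 62 per arm, 124 in total.
- Check: 982 × 0.75 = 736.5 per arm.

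**Step 3. What the stated target leaves after 25% loss**

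- 920 × 0.75 = 690 per arm, 1,380 in total.
- Short of requirement: 736 − 690 = 46 per arm, 92 in total.
- Largest loss that still leaves 736: 1 − 736/920 = 20%.

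**Step 4. Effect on power**

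Without a mean and standard deviation, the 736 cannot be checked. The standardised difference it implies can be recovered:

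- d = (1.960 + 1.2816) × √(2/736) = 3.2415 × √(2/736) = 0.169.
- For a 20% reduction, this means a standard deviation of about 0.2/0.169 = 1.18 times the control mean.

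Power with n per arm is Φ(d × √(n/2) − 1.96):

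| Loss from 920 | Remaining per arm | Power (two-sided 5%) |
|---|---|---|
| 20% | 736 | 90.0% |
| 22% | about 718 | about 89.3% |
| 25% | 690 | 88.1% |

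If the 5% is one-sided, the implied d is 0.153 and power at 690 is 88.3%.

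**Step 5. Detectable effect**

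For 90% power with 690 per arm, the detectable reduction is 20% × √(736/690) = 20.7%.

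**The case against.** The arithmetic itself cannot be contested, and no other section corrects it. Five points can be made about its weight and wording.

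- **Size.** The worst case costs about two points of power, and only at the very top of an up-to-25% range. This is correct, and the point should not be presented as a threat to the trial.
- **Cause.** Since 920 equals both 736 × 1.25 and 736/0.80, the document cannot show whether a wrong inflation formula was used or a correct calculation for 20% loss was mislabelled as 25%. This also stands. The first is a familiar slip, but all that can be asserted is that 736, 25% and 920 are incompatible.
- **Where the power claim is attached.** The 90% is tied to 736 at follow-up, so anyone counting 690 would see the shortfall. That is true after the fact, but by then recruitment is closed. The purpose of the randomisation target is to prevent the shortfall.
- **Covariate adjustment.** The Analyses section adjusts for baseline AUDIT-C. If 736 was derived without adjustment, a correlation of 0.25 between AUDIT-C and the outcome would offset the loss, since 736 × (1 − 0.0625) = 690. The protocol gives neither the correlation nor the basis of the 736, so this makes the 88.1% approximate without repairing the contradiction.
- **Abstract.** The 1,472 is not wrong, and abstracts condense. Adding the number randomised is a helpful clarification, not the correction of an error.

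The promised efforts to limit loss make 25% less likely, but do not change what 25% loss would leave.

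**Conclusion.** The concern holds. As written, the randomisation target delivers the 736 per arm needed for 90% power only up to 20% loss, not the 25% claimed. Meeting the claim would take 982 per arm (1,964 in total) instead of 920 (1,840). This conclusion rests only on 736, 25% and 920, all of which the protocol states.

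The practical consequence is modest: about 88% power at the full 25% loss, and none at 20% or below. The power figure assumes a two-sided 5% test, an unadjusted comparison of two means, and the standardised difference implied by the protocol's own 736. Whether the formula or the percentage is at fault cannot be determined from the document. Because a headline design figure for the primary outcome is wrong, it should be corrected despite the small effect.

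**What to change.** Preferred: keep 920 per arm and correct the sentence in the Sample size section, for example: with up to 20% loss, randomising 920 per arm (1,840 in total) leaves 736 per arm for analysis; with 25% loss, 690 per arm would remain, giving about 88% power. In the abstract, give both figures: 1,840 randomised and 1,472 with 3-month data.

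This costs two sentences and no extra participants. The stated tolerance becomes slightly less favourable.

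Alternative: if a 25% tolerance at 90% power must be kept, state 982 per arm (1,964 in total), which is 124 more participants than now planned.

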### Analyses

Analyses will compare outcomes between groups at three months following the intention to treat principle. The principal analysis will be conducted using a generalised linear model with identity link and Gaussian error. The baseline AUDIT-C score will be included as a patient level explanatory variable, along with a classification variable for workplace and for randomised group. Analogous models will be conducted for secondary outcomes. We will conduct an additional prognostic model examining subject and organisational factors (and potential interactions) associated with the size of any treatment effect. For the economic evaluation we will design a decision analytical model in line with National Institute of Health and Clinical Excellence (NICE) guidance to determine the incremental cost per quality adjusted life year (QALY) gained, calculated using the EQ-5D, and cost per reduction in units of alcohol consumed of the web-based screening and brief intervention compared to web-based screening alone at 3 months, 12 months and 10 years. As participants in the control group will be referred to DYD at 3 months, the 12 month analysis for the control group will assume that the costs and outcomes for the first 3 months of the trial would have continued for the next 9 months had they not received the intervention at 3 months. Effectively, costs and outcomes over 12 months for the control group will be cost and outcomes for the first 3 months multiplied by 4. Published data will be used for the 10 year model and all costs and outcomes will be discounted in accordance with NICE guidance. The primary cost- effectiveness analysis will be from the perspective of the NHS with a secondary cost-offset analysis from the perspective of the employer. Costs to the NHS will include the costs of hospital admissions. Unit costs will be taken from standard published sources such as Personal Social Services Research Unit (PSSRU) [32]. The cost to the employer will include the cost of implementing web based screening and brief intervention and the cost of the time it takes employees to complete web based screening and brief intervention. This will be offset by any cost savings associated with reduced number of days of sick leave for the screening and brief intervention group compared to the screening only group. We are aware of the potential seasonal variation in sickness absence and will address this in the sensitivity analyses. Analyses will be subject to deterministic and probabilistic sensitivity analyses. Modelling will be used to explore the relative cost-effectiveness of primary care versus work-place SBI.

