### Setting

A large UK-based employer with an international workforce of approximately 100,000 has agreed to participate. This employer has a socially diverse workforce with a presence in the UK, Europe, North America, Australasia, Africa and the Middle East. The company has an active health promotion / occupational health programme with a regular series of health promotion campaigns and road shows. All employees have a work-related email address and most of the internal communication within the company is undertaken online.

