### Data collection

Baseline data collection will be integrated into the initial online health check questionnaire. This will include: year of birth, gender, occupational classification, height, weight, smoking status, dietary consumption of fruit and vegetables (portions per day), level of physical activity (minutes per week of vigorous, moderate and mild activity), frequency of consuming alcohol, average consumption on a drinking day, and frequency of drinking more than 6 drinks on one occasion (AUDIT-C), and health related quality of life (EQ-5D). Instruments for collecting data on hospital admissions will be those used in the SIPS and AESOPS trials of screening and brief intervention in multiple settings [29-31].

Follow-up data collection will be undertaken online. At follow-up participants will be asked to complete the TOT-AL, AUDIT, EQ-5D, report the number of days of sickness absence in the past 3 months and number and duration of any hospital admissions.

Data on numbers of health checks completed and proportion of employees scoring 5 or more on the AUDIT-C will be recorded. Use of DYD, including pages visited will be recorded using Google analytic software.

Data on costs of the intervention will be estimated from the costs incurred in the trial (separating out trial costs from intervention costs) for preparatory communications with stakeholders, preparing the invitations, developing the online health check, developing the tailored feedback, applying the software to provide tailored feedback, and updating.

Follow-up rates will be maximised by sending up to three e-mail requests for data. Non-responders will be contacted by post and phone to see if they received the e-mail reminders and request online completion. Participants who do not respond to these requests will be sent a final email and / or phoned asking just for primary outcome data (amount of alcohol consumed in past 7 days).

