### Baseline data collection

Collecting baseline data on alcohol consumption would increase the power of the study, as it would allow for determination of individual change. However, alcohol consumption is notoriously sensitive to assessment, with simple measurement of past week alcohol consumption or completion of the Alcohol Use Disorders Identification Test (AUDIT) resulting in a decrease in consumption of about 20% [34]. This reactivity of assessment is thought to be a contributing factor to the lack of difference seen in many alcohol trials [35] and for this reason, we decided against collecting baseline data on alcohol consumption.

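### Baseline items already collected (EQ-5D, drinking frequency and quantity, sex, age) could sharpen the stated models at almost no cost

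*Protocol article*

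**What the plan says.** The Analyses section fixes the form of the primary model: "The principal analysis will be conducted using a generalised linear model with identity link and Gaussian error". It then names the explanatory variables: "The baseline AUDIT-C score will be included as a patient level explanatory variable, along with a classification variable for workplace and for randomised group". For the other outcomes it says: "Analogous models will be conducted for secondary outcomes". The Abstract lists EQ-5D among the secondary outcomes, and Analyses derives the QALYs from it.

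The Data collection section shows what is available at baseline. The drinking items are "frequency of consuming alcohol, average consumption on a drinking day, and frequency of drinking more than 6 drinks on one occasion (AUDIT-C". Also recorded are "year of birth, gender, occupational classification, height, weight, smoking status" and, at the end of the list, "and health related quality of life (EQ-5D".

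In the Discussion, under Baseline data collection, the article remarks: "Collecting baseline data on alcohol consumption would increase the power of the study". It explains that such data were left out on purpose, because measuring past-week drinking or giving the full AUDIT can itself lower consumption.

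**The concern.** The primary outcome is an amount: past-week consumption by the TOT-AL. Weekly amount is frequency multiplied by quantity, whereas the AUDIT-C score adds ordinal codes for frequency, quantity and heavy episodes. Someone who drinks often but little can share a score with someone who drinks seldom but heavily. Selection at a score of 5 or more also cuts off the lower part of the score's range. A baseline index closer to the scale of the outcome can be built from answers that every participant has already given. It asks nothing new of participants, so the reactivity argument in the Discussion does not count against it.

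For EQ-5D the named baseline covariate is an alcohol score, a weak stand-in for baseline utility, although baseline utility itself is recorded. At stake are the width of the confidence interval for the primary outcome, and the precision of the QALY difference together with its exposure to chance baseline imbalance.

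**Working it through.** **Inputs.** From Sample size: 736 per arm analysed, 90% power, 5% significance, 20% reduction. The article gives no control mean, SD, sidedness or R-squared, so 736 cannot be reproduced from stated inputs. It can only be solved backwards.

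**Step 1: what 736 implies** (normal approximation, equal arms).

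Standardised effect d = (z for alpha + z for power) × √(2/n).

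- Two-sided: d = (1.960 + 1.282) × √(2/736) = 3.2415 × 0.05213 = 0.169, so SD/mean = 0.20/0.169 = 1.18.
- One-sided: d = (1.645 + 1.282) × 0.05213 = 0.153, so SD/mean = 1.31.

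**Step 2: how much the index adds to the score.** This was simulated: assumed distributions of frequency and quantity, AUDIT-C items formed by assumed cut-points, and restriction to a score of 5 or more. The reported quantity is the fall in residual variance when the frequency × quantity index joins the summed score.

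| SD/mean of past-week drinking | Fall in residual variance |
|---|---|
| 1.0–1.1 | 22–25% |
| 1.3–1.4 | 10–11% |
| about 2 | 4–5% |

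Other assumed distributions gave 16% and 26% at SD/mean about 1.0, 19% at 0.9, 6% and 13% at about 1.35, 7% and 9% at about 1.5, and 2–4% at 1.8 and above. In one of these simulations, among people scoring 6, the 5th to 95th percentile of the index ran from about 2–4 up to 19 drinks per week. That spread is what the sum hides. No separate gain was worked out for sex and age.

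**Step 3: effect on power at 736 per arm.** Take 90% as the power under the planned model, two-sided, and let f be the proportional fall in residual variance.

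Power = Φ(3.2415/√(1 − f) − 1.960). Equivalent n per arm = 736 × (1 − f).

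| f | 3.2415/√(1 − f) | Power | Equivalent n per arm | Interval width ratio √(1 − f) |
|---|---|---|---|---|
| 0 | 3.242 | 90.0% | 736 | 1.000 |
| 0.02 | 3.274 | 90.6% | 722 | 0.990 |
| 0.05 | 3.326 | 91.4% | 700 | 0.975 |
| 0.10 | 3.417 | 92.7% | 663 | 0.949 |
| 0.25 | 3.743 | 96.3% | 552 | 0.866 |

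**Step 4: EQ-5D.** The article does not say how the 3-month QALY is formed. Suppose, as an assumption, that it is the area under a straight line between baseline and 3 months. If mean baseline utility in the control group is lower by δ through chance, baseline alone contributes 0.25 × δ/2 = 0.125δ to the QALY difference, before any carry-over into 3-month utility. Analyses then multiplies the control group's 3-month outcomes by 4 for the 12-month analysis, which turns that into 0.5δ on the control side. Including baseline EQ-5D as a covariate adjusts for the observed imbalance. It also reduces residual variance by the share that baseline utility explains beyond AUDIT-C, a figure that the article does not give.

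**The case against.** The strongest reply is that nothing here is wrong. A short, pre-specified covariate set leaves the randomised comparison valid. Frequency and quantity already enter through the score, so the argument is about a sum versus a product. The gain cannot be read from the document: 2% and 25% are both obtainable, depending on what is assumed about week-to-week noise. An analysis plan that is not shown may add covariates. An analogous model for EQ-5D could even be read as one that uses EQ-5D's own baseline.

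Most of this stands, and it limits the point to an improvement. It does not remove it. Analyses does name the covariates, the simulations show that the sum does not use all the information in its items, and the wording on secondary outcomes does not settle which baseline value is meant.

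A reader might infer more than the document supports:

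- *That the article admits a lack of precision.* It does not. It claims 90% power, and says only that a measure it deliberately chose not to take would have added power.
- *That AUDIT-C is the only adjustment.* Workplace is also in the model.
- *That workplace is an empty term.* Setting describes one employer ("A large UK-based employer with an international workforce of approximately 100,000 has agreed to participate"), but the Abstract speaks of employers in the plural, and the term could mean site. Swapping it for country or region is not supported, because neither is listed among the baseline items.
- *That leaving out baseline EQ-5D biases the QALY difference.* Under randomisation, chance imbalance is not bias in expectation.
- *That better adjustment is needed to make up for dropout.* Sample size allows for 25% loss by taking 736 × 1.25 = 920, which leaves 920 × 0.75 = 690. That is a separate matter and should be judged by itself.

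**Conclusion.** The point holds as an efficiency improvement of modest priority. The planned analysis is valid, and no figure in the article is shown to be wrong by it. The baseline EQ-5D term is the clearer part: the variable is collected, it is the baseline of the outcome itself, and the adjustment corrects for any chance imbalance in baseline utility.

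For the primary outcome the direction of the gain is plausible but its size is assumed. The expected fall in residual variance is roughly 4–5% with very noisy weeks (SD/mean about 2), up to about 25% at SD/mean about 1. A fall of 5–10% takes power at 736 per arm from 90% to about 91–93%. This rests on the assumed drinking distributions and item cut-points, a two-sided test, and 90% being the power under the model as planned. The implied SD/mean of 1.18 (1.31 if one-sided) lies where the simulated gain is not trivial, but that ratio is itself solved backwards from 736.

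**What to change.** Pre-specify the following before unblinding:

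1. In the EQ-5D and QALY comparison, include baseline EQ-5D as a covariate, so that the analogous model is explicit about which baseline value it uses.
2. In the primary model, keep the AUDIT-C score and the workplace term. Add a baseline frequency × quantity index, in drinks per week, built from the midpoints of the AUDIT-C response categories. Add sex and age (from year of birth).

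This costs a sentence or two in the analysis section. It needs no new data and puts no extra burden on participants. The small downsides are a few more model terms and an index that is only approximate, because it rests on category midpoints. Keeping the summed score in the model means that nothing already planned is lost.

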### Outcomes

Outcomes have been selected to reflect the aims and objectives of the trial. Hence the primary outcome is past week alcohol consumption, measured by the TOT-AL [26]. This is an on-line measure of past week alcohol consumption that was developed for use in the online trial of *Down Your Drink* and has been validated in a UK population.

Secondary outcomes include:

The number of employees completing the online health check;

The number (proportion) of employees who complete the online health check and score 5 or more on the AUDIT-C;

The number (proportion) of participants in the intervention group who access DYD at least once;

Alcohol use disorders, measured by the AUDIT [4]. This will allow comparison of our data with other alcohol trials;

Outcomes for economic evaluation include:

Health state, measured by the EQ-5D [27];

Number of days of sickness absence in past 3 months (self-reported)[28];

Number and duration of hospital admissions in past 3 months (self-reported);

Costs, staff time and resources required to implement intervention

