### Comparator and duration of follow-up

The trial uses a wait list design, with the comparator group receiving no feedback on their alcohol consumption until they have completed data collection at the primary outcome point (3 months). We consider this is ethical as a) this is a non-help seeking population; b) the time-course of alcohol misuse is long (many years) and it is unlikely that three months delay in provision of feedback and advice is likely materially to alter outcomes; and c) all participants are advised to consult their GP if they have any concerns about their health. We had initially considered a 12 month primary outcome point but decided this was potentially unethical as 12 months delay could potentially be harmful. Moreover, our procedures had to be acceptable to the collaborating workplace, which had indicated that a three month follow-up period was the longest they would consider acceptable. Our previous work had suggested that reductions in alcohol consumption seen at 3 months were maintained at 12 months [33], although the data from that trial may not apply to the different population recruited here.

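### The 12-month economic rule multiplies all control-arm costs and outcomes by 4 without separating one-off from recurrent items, and no 12-month assumption is stated for the intervention arm

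*Protocol article*

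**What the plan says.** The Analyses section of the protocol article promises two ratios, the "incremental cost per quality adjusted life year (QALY) gained, calculated using the EQ-5D" and the "cost per reduction in units of alcohol consumed", for screening with brief intervention "compared to web-based screening alone at 3 months, 12 months and 10 years".

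For the 12-month horizon it gives a rule for one arm. The sentence opens "As participants in the control group will be referred to DYD at 3 months, the 12 month analysis for the control group will assume" and goes on to say that the costs and outcomes of the first 3 months "would have continued for the next 9 months had they not received the intervention at 3 months". The rule is then put into practice: "Effectively, costs and outcomes over 12 months for the control group will be cost and outcomes for the first 3 months multiplied by 4".

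Other sections bear on this:
- Data collection and Follow-up describe one follow-up point, at 3 months. Comparator and duration of follow-up explains that, for the workplace, "a three month follow-up period was the longest they would consider acceptable".
- EQ-5D is collected at baseline and at 3 months (Data collection).
- For alcohol, "the primary outcome is past week alcohol consumption, measured by the TOT-AL". Past-week consumption is deliberately not measured at baseline (Baseline data collection).
- The primary perspective is the NHS, and hospital admissions are the only cost named there. Implementation cost and employees' completion time are named under the secondary employer perspective (Analyses).
- Published data are assigned to the 10-year model. No source is named for months 3 to 12.

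**The concern.** A 12-month incremental ratio needs 12-month costs and outcomes in both arms. Here neither arm is observed beyond 3 months, yet an extrapolation is written down for the control arm only. The reader cannot tell what the scaled control arm will be compared with.

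The control-arm rule also covers everything without exception. The comparator is screening alone, so whatever screening costs per participant can fall in that arm, and screening happens once. A blanket multiplier treats it as if it recurred every quarter. EQ-5D is a state rather than a running total, so multiplying a 3-month QALY total by 4 is not in general the same as assuming that the state reached at 3 months continues.

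At stake is the 12-month result, one of three economic horizons.

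**Working it through.** **The plan's figure.** 12 months / 3 months = 4, and 13 weeks × 4 = 52 weeks. The multiplier is the correct ratio of the two periods. The question is which quantities it may be applied to. The protocol gives no cost, EQ-5D or consumption values, so what follows is algebra with assumed values, marked as such.

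**Costs, control arm.** Let c be a one-off cost per participant (screening, completion time) and r the recurrent cost per quarter (admissions, or sickness days for the employer).
- Rule as written: 4(c + r) = 4c + 4r.
- One-off cost counted once: c + 4r.
- Excess: 3c. For assumed c of £5, £10 and £20 this is £15, £30 and £60.
- If c = 0, the rule is exact.

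**Incremental cost.** Let i be the extra one-off cost of the brief intervention, with recurrent costs equal in the two arms. Assume c = 5, i = 5, r = 50.
- One-off costs counted once in both arms: (5 + 5 + 200) − (5 + 200) = 210 − 205 = +5.
- Control arm × 4, intervention arm's one-off costs counted once: 210 − 4(5 + 50) = 210 − 220 = −10, in general i − 3c.
- Both arms × 4: 4(5 + 5 + 50) − 220 = 240 − 220 = +20, in general 4i.

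The incremental cost is thus understated or overstated according to a choice that the article does not state.

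**QALYs.** Let u0 and u3 be EQ-5D at baseline and 3 months, and suppose QALYs are computed as area under the curve (the article does not name the method).
- First quarter: 0.25(u0 + u3)/2.
- Rule: 4 × 0.25(u0 + u3)/2 = 0.5u0 + 0.5u3.
- 3-month state carried forward: 0.25(u0 + u3)/2 + 0.75u3 = 0.125u0 + 0.875u3.
- Rule minus carry-forward: 0.375(u0 − u3).

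With assumed u0 = 0.85 and u3 = 0.87, the rule gives 0.8600 and carry-forward 0.8675, a difference of 0.0075 in size. For an assumed change of 0.05 the size is 0.375 × 0.05 = 0.01875. With no change it is zero.

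**Units of alcohol.** Let w be the past-week total. Cumulated over the quarter it is 13w, and 13w × 4 = 52w, which is a year. The rule is exact for a 13-week total.

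**The case against.** The best defence is that the operative statement is the steady-state assumption, and that multiplying by 4 only paraphrases it. On that reading steady recurrent items scale correctly. The control arm gets special mention for a reason: it is referred to the intervention at 3 months, so its later course has to be a counterfactual, whereas the intervention arm has no such crossover. The intervention arm's extrapolation would sit in the decision model, whose inputs a condensed article may leave to a fuller plan, and deterministic and probabilistic sensitivity analyses are promised. Screening is common to both arms and cancels if treated alike.

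Much of this stands, and it rules out several stronger readings that a reader might infer:
- *That alcohol consumption is understated 13-fold.* This would need a single week's figure to be multiplied by 4 and called a year (for an assumed 20 units a week, 80 instead of 1,040). The text speaks of outcomes for the first 3 months, which can be read as a 13-week total.
- *That QALYs are wrong in any case.* A 3-month QALY total times 4 has the right dimension and is exact if EQ-5D is stable. The control arm receives no alcohol feedback before 3 months, so the documents give no reason to expect a large change.
- *That the rule favours the intervention.* This needs the intervention arm's one-off costs to be counted once, which is not stated. Multiplying both arms reverses the sign of the error.
- *That the authors suppose the intervention arm is observed to 12 months.* The text does not say so. It is only silent on that arm.

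Three things remain. The multiplier is stated for all control-arm costs, with no exception. The cancellation argument does not rescue it: if both arms are multiplied, c cancels but the intervention's own one-off cost is charged as 4i. And varying the inputs in sensitivity analyses neither corrects a one-off item counted four times in the base case nor supplies the missing assumption. The remark in Comparator and duration of follow-up that reductions persisted to 12 months in an earlier trial carries its own caveat about this population and is not adopted as the rule.

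**Conclusion.** The point holds in a limited form. As written, the 12-month rule overcharges any one-off control-arm cost c by 3c, and the comparison cannot be determined from the article because no assumption is given for the intervention arm. With the assumed costs above, the incremental cost is −10 or +20 against +5, so the direction of bias is open.

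The one-off error matters mainly in the secondary employer analysis. It reaches the primary NHS analysis only if screening costs are charged there, which the article neither states nor excludes. The QALY discrepancy is conditional on an area-under-the-curve calculation and on a change in EQ-5D. A fuller plan may state the intervention-arm assumption, but the published control-arm sentence would still need correcting.

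This is worth correcting before the economic analysis, but it is not a threat to the trial: randomisation, data collection and the 3-month comparison are untouched.

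**What to change.** Replace the multiply-by-4 sentence in Analyses with one 12-month rule that applies to both arms:
- Count one-off costs (set-up, screening, feedback, access to the intervention, completion time) once.
- Continue recurrent items (admissions, sickness days) at the 3-month rate.
- Compute QALYs as the observed 3-month area plus 0.75 × the 3-month EQ-5D, so that the 3-month state is carried over the remaining 39 weeks.
- Carry weekly units over the same 39 weeks, and say how the past-week figure is turned into a total for the first 13 weeks.
- Add sensitivity scenarios in which the between-arm effect persists, or decays to zero, between 3 and 12 months.

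If a different assumption is wanted for the intervention arm, state it explicitly beside the control-arm one. The cost is rewording and a few lines in the model, plus a little work for the scenarios. No new data are needed.
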